## Abstract

**Background:**

Epidermal growth factor receptor tyrosine kinase inhibitors (EGFR-TKIs) are widely used in the treatment of non–small cell lung cancer due to their precision, efficiency, and ease of use. However, skin rashes induced by EGFR-TKIs are the most common and earliest form of skin toxicity, often affecting the quality of life and treatment compliance of patients and leading to early discontinuation of therapy. These skin reactions may even impact cancer outcomes. In clinical practice, traditional Chinese medicine detoxification granules have shown effectiveness in relieving skin discomforts such as itching, pain, and burning caused by EGFR-TKI therapy. A prior single-arm trial investigating the treatment of targeted drug–induced rashes demonstrated a sustained improvement in rash symptoms with an effectiveness rate of 80.77% and was well tolerated by patients.

**Objective:**

As an exploratory clinical study, this randomized controlled trial will preliminarily evaluate the potential efficacy and safety of jiedu xiaozhen (JDXZ) granules in managing EGFR-TKI–related skin toxicities.

**Methods:**

This randomized controlled trial will be conducted at Shanxi Provincial Hospital of Traditional Chinese Medicine. A total of 94 patients with confirmed epidermal growth factor receptor gene–mutated non–small cell lung cancer who developed rashes after EGFR-TKI treatment will be enrolled. Patients will be randomly assigned to either a JDXZ traditional Chinese medicine group (group J) or a urea ointment group (group U). The primary outcome will be the severity of the rash as assessed using the National Cancer Institute Common Terminology Criteria for Adverse Events grading. Secondary outcomes will include the WoMo (Wollenberg and Moosmann) score, numerical rating scale, Dermatology Life Quality Index scale, European Organisation for Research and Treatment of Cancer Quality of Life Questionnaire Core 30 score, median progression-free survival, and changes in the levels of fibroblast growth factor 7 and hepatocyte growth factor in the blood. Adverse reactions will be recorded throughout the study. Data will be analyzed using SPSS.

**Results:**

The clinical trial registration was completed in October 2024. This study is currently underway. As of December 1, 2025, a total of 81 eligible participants had been enrolled, all of whom were assigned to groups following the randomization principle. Among them, 42 participants were allocated to the JDXZ group (with an additional 2 participants pending enrollment), and 39 to the control group. Based on the current progress, the estimated trial completion date has been extended to January 31, 2026.

**Conclusions:**

The results of this study may help develop an effective treatment for EGFR-TKI–mediated rashes. The findings will be published in academic journals upon the completion of the trial.

## Introduction

Patients with non–small cell lung cancer (NSCLC) who harbor epidermal growth factor receptor (*EGFR*) mutations represent a unique subgroup [1]. Women, nonsmokers, and patients with adenocarcinoma are more likely to carry *EGFR* mutations, with an incidence of 30% to 35% in East Asian populations [2]. In the Chinese NSCLC population, the prevalence of *EGFR* mutations is 28.2%, rising to 50.2% in those with lung adenocarcinoma [3]. *EGFR* tyrosine kinase inhibitors (EGFR-TKIs) selectively block the *EGFR* signaling pathway, thereby improving survival in patients with NSCLC carrying *EGFR* mutations [4]. It is categorically endorsed as a grade IA recommendation for the postoperative, locally advanced, and advanced first-line treatment of EGFR-positive NSCLC [5]. However, as *EGFR* is also expressed in skin keratinocytes, sebaceous glands, hair follicles, and perinuclear tissues [6], inhibiting *EGFR* activity can trigger a cascade of intracellular signaling pathways. The integrity of the human epidermis is compromised, the proliferation of epidermal cells is perturbed, the sebaceous gland lipid secretion is disrupted, and the skin’s hydration retention function is impaired, culminating in the manifestation of adverse cutaneous reactions [7].

According to phase 3 clinical trials approved by the US Food and Drug Administration, the incidence of skin rash associated with gefitinib use was 66% in patients from East Asia, whereas 3.1% experienced grade 3 rashes. Erlotinib use resulted in a 73% rash incidence, with 32% being grade 3; afatinib use led to rashes in 80.8% of patients, with 14.6% experiencing grade 3 rashes. In China, icotinib use caused rashes in 15.5% of patients, with 14.9% experiencing grade 3 rashes [8]. Results from the FLAURA2 trial found that the incidence of grade 3 adverse effects was higher in the combination therapy group than in the monotherapy group (ranging from 11% to 54%), with serious adverse effects increasing from 5% to 19%. Osimertinib, another EGFR-TKI, was associated with skin toxicity in approximately 24% of patients [9].

The most common and earliest cutaneous side effects of anti-*EGFR* therapies are papules and pustules distributed in seborrheic areas such as the face, scalp, and upper trunk, sometimes extending to the limbs, palms, and soles. These reactions typically occur within 1 to 2 weeks of starting targeted therapy and are dose dependent. It is noteworthy that this issue is encountered in a minimum of 75% of the patient population [10]. The severity of the rash is often positively correlated with the response to treatment of the patients [11]. Approximately 35% of patients initially manifest dry, pruritic dermatitis affecting the extremities [12,13]. The onset of sebum deficiency in eczema is typically concurrent with the exacerbation of the condition, culminating in a pustular rash secondary to either *Staphylococcus aureus* or herpes simplex infection [14], which may or may not be accompanied by hyperpigmentation and telangiectasia [15]. Unlike acne vulgaris [16], these skin reactions are characterized by erythematous papules and pustules without acne or cysts. Other associated symptoms include dry skin, burning sensations, itching, pain, and changes to the hair and nails (eg, paronychia) [17]. To manage these side effects, patients should avoid contact with irritants, particularly in areas prone to rashes. Daily skin care should include the use of moisturizers and sun protection and the avoidance of extreme temperatures. Wearing comfortable clothing and shoes and using nonirritating bath products is also recommended [18]. It is imperative to mitigate the adverse cutaneous reactions that are elicited.

At present, the assessment of targeted drug–induced cutaneous toxicities is conducted in accordance with the 2017 National Cancer Institute Common Terminology Criteria for Adverse Events (NCI-CTCAE). Various guidelines, including those from the Multinational Association of Supportive Care in Cancer skin toxicity study group, the National Comprehensive Cancer Network, and the European Society for Medical Oncology, offer different expert opinions and consensuses on managing skin toxicity [11,19-21]. However, these guidelines lack comprehensive, evidence-based recommendations [8,10]. As patients often experience dry, itchy skin that compromises their skin barrier, most treatment strategies focus on symptom relief, and there are discrepancies in clinical practice regarding medication use [8,10].

The dermatological adverse effects associated with *EGFR* inhibitors are transient and tend to diminish with extended treatment duration. Resolution of the rash is typically complete upon cessation of therapy, and it is seldom constrained by the dosage or duration of treatment. Xerosis and pruritus are commonly attributable to a compromised skin barrier function. The predominant therapeutic modalities used for the management of grade 1 or 2 cutaneous toxicity encompass topical treatments such as 2.5% hydrocortisone cream, topical antibiotics (including erythromycin cream, clindamycin emulsion, metronidazole cream, and tacrolimus cream), and moisturizers (such as urea cream and fusidic acid cream). For more severe cases, oral medications may be considered, such as doxycycline (100 mg twice daily) or minocycline (50‐100 mg twice daily). Oral antihistamines, including levocetirizine (5 mg daily), desloratadine (5 mg daily), diphenhydramine (25‐50 mg 3 times daily), hydroxyzine (25 mg 3 times daily), or fexofenadine (60 mg 3 times daily), can help manage pruritus. For grade 3 rashes, oral tretinoic acid (0.3‐0.5 mg per kilogram) or prednisone (0.5 mg per kilogram) may be prescribed. Gamma-aminobutyric acid receptor agonists such as gabapentin (300 mg every 8 hours) or pregabalin (50‐75 mg every 8 hours) can also be considered for symptom relief. In severe cases, the dosage of targeted drugs should be reduced according to clinical guidelines, and for grade 4 rashes, oral steroid use may be escalated, and targeted therapy should be discontinued as soon as possible. Additionally, other studies have explored alternative treatments. For example, a study by Nagase et al [22] found that rapid desensitization therapy was effective in treating severe rashes caused by molecularly targeted drugs in patients with NSCLC. Furthermore, vitamin K_1_ has shown potential in preventing rashes associated with *EGFR* inhibitors, possibly reducing both the incidence and severity of acne-like rashes [18,21].

Retinoic acid drugs are commonly used in clinical practice, but higher doses can exacerbate skin and mucosal dryness. Additionally, due to their photosensitivity, patients need to avoid radiation exposure as these factors can worsen rashes [23]. Doxycycline has been found to reduce the severity of rashes induced by EGFR-TKIs [18]. However, in clinical practice, doxycycline and minocycline are not frequently used for treatment; instead, they are primarily used in preventive studies [18,24-26]. The findings of Deplanque et al [25] also confirmed that, while doxycycline may not lower the incidence of erlotinib-induced folliculitis, it does reduce the severity of the rash. It is important to note the potential side effects of tetracycline antibiotics, which include anorexia, nausea, vomiting, diarrhea, esophagitis, and esophageal ulcers [27]. Systemic steroid hormones are usually not the first line of treatment for *EGFR* inhibitor–associated rashes due to their own side effects [19], such as endocrine disorders, osteoporosis, and weakened immunity, which can have serious consequences [28].

Due to the complex nature of infections and the standardized use of antibiotics, it is important to remain vigilant about antibiotic resistance. Glucocorticoids, while potent in treating skin toxicity, should only be considered when other treatment options are ineffective, making both antibiotic therapy and glucocorticoid therapy less ideal for routine clinical use. Patients receiving molecular-targeted therapies are often highly sensitive to irritants and allergens, complicating clinical treatment decisions. Most of the patients with lung cancer and *EGFR* mutations who experience cutaneous adverse reactions to EGFR-TKIs do not seek treatment due to a lack of awareness of or confidence in existing treatment options. Research reveals that EGFR-TKI skin toxicity stems from a compromised skin barrier linked to abnormal keratinocyte differentiation, apoptosis, and inflammatory infiltration [29]. To guarantee the rational deployment and therapeutic efficacy of clinical pharmacotherapy, it is advisable to use mild emollients, which incorporate active constituents such as urea, ceramide, plant sterols, and linolenic acid, among others, for the purpose of local hydration; moisturization; anti-inflammatory action; antipruritic effects; and amelioration of cutaneous symptoms such as dryness, itching, and pain [29]. Consequently, the identification of novel and well-tolerated therapeutic modalities to address drug-induced dermatotoxicity continues to pose a significant challenge for the oncological community.

Traditional Chinese medicine (TCM) active ingredients and preparations are increasingly used in skin disease treatment as modern pharmacology and clinical trials advance [30]. Jiedu xiaozhen (JDXZ) granules, a blend of *Astragalus membranaceus*, *Isatis indigotica Fort*, and *Concha margaritifera*, show promise in managing EGFR-TKI–induced skin toxicity. Author LL, with 40 years’ experience in TCM, has shown JDXZ granules’ efficacy and safety for treating EGFR-TKI–related skin toxicity. The oral JDXZ granules in their single-arm trial [31] effectively alleviated systemic symptoms, sustaining rash improvement and reducing posttargeting recurrence with minimal side effects. In clinical observation, targeted drug–related skin toxicity showed sustained improvement with an effectiveness rate of 80.77% and was well tolerated by patients. This exploratory randomized controlled trial (RCT) will preliminarily evaluate the efficacy and safety of JDXZ granules to explore a potential management strategy for skin toxicity induced by EGFR-TKIs.

## Methods

### Study Design

This study is a multicenter, prospective, randomized controlled clinical trial in which participants will receive either enhanced TCM or positive control drugs. The trial will involve 94 patients with a confirmed diagnosis of *EGFR* gene mutation–positive NSCLC who developed skin rashes after using EGFR-TKIs. The participants will be divided into 2 groups: the treatment group (receiving oral JDXZ granules) and the control group (receiving topical urea ointment). Effectiveness will be assessed by comparing baseline conditions with the results at 2 weeks after treatment. Each patient will undergo 4 scheduled visits: at baseline and on days 3, 7, and 14 (Figure 1).

**Figure 1. F1:**
[figure not shown]
Clinical trial flowchart. CRF: case report form; DLQI: Dermatology Life Quality Index; EORTC QLQ-C30: European Organisation for Research and Treatment of Cancer Quality of Life Questionnaire Core 30; JDXZ: jiedu xiaozhen; laboratory examination: changes in blood levels of factors such as fibroblast growth factor 7 and hepatocyte growth factor; NCI-CTCAE: National Cancer Institute Common Terminology Criteria for Adverse Events; NRS: numerical rating scale; PFS: progression-free survival (time during which patients remain free from disease progression; follow-up every 3 months); TCM: traditional Chinese medicine; WoMo (Wollenberg and Moosmann) score: ranges from 0 to 100 and is calculated using the formula final score=1/4A + 1/4B + 10/3C).

### Study Setting

Participants will be recruited from 3 centers: Shanxi Provincial Hospital of Traditional Chinese Medicine, Shanxi Cancer Hospital, and the Second Affiliated Hospital of Shanxi Medical University. Adequate sample sizes will be obtained through various hospital departments and online platforms. Inclusion criteria will be verified, ensuring that participants have relatively complete medical records and have signed the informed consent form.

### Participants

#### Recruitment Strategy

Patients will be enrolled from 3 clinical centers, most of which have been designated as affiliated hospitals of the Lung Cancer Mutation Consortium. Recruitment advertisements will be posted in hospital bulletins, social media, and medical forums. The enrollment procedure will be streamlined to facilitate expeditious and hassle-free completion by the patients, thereby mitigating potential obstacles to their participation.

#### Eligibility Criteria

##### Inclusion Criteria

Inclusion criteria are as follows: (1) patients diagnosed with NSCLC carrying *EGFR* gene mutations who have developed skin rashes following EGFR-TKI treatment, with rash severity graded as 1 to 3 according to the NCI-CTCAE 5.0 standards; (2) patients aged ≥18 years, with no gender restrictions, and who have a Karnofsky Performance Status score of at least 60; (3) patients with adequate hematological, hepatic, renal, and metabolic function as indicated by specific blood count and organ function parameters (white blood cells of >3 × 10^9^ per liter, absolute neutrophil count of ≥1.5 × 10^9^ per liter, platelet count of ≥100 × 10^9^ per liter, hemoglobin of >9 g/dL, serum creatinine of ≤1.5 times the upper limit of normal [ULN], bilirubin of ≤1.5 times the ULN, aspartate aminotransferase or alanine transaminase of ≤2.5 times the ULN, if liver metastases are present, AST/ALT ≤ 5 × ULN, and serum electrolyte within normal range); and (4) patients who are willing to receive the study treatment and sign the informed consent form with good compliance.

##### Exclusion Criteria

Exclusion criteria are as follows: (1) impaired visceral function; (2) a history of significant cardiovascular diseases (including myocardial infarction, unstable angina pectoris, symptomatic congestive heart failure, and severe uncontrolled arrhythmia) within the previous year, interstitial lung disease (such as pneumonia or pulmonary fibrosis), or evidence of interstitial lung disease on a baseline chest computerized tomography scan; (3) concurrent antitumor treatments; (4) rashes unrelated to EGFR-TKI drugs or recent rash-related treatments; (5) participation in other clinical trials within 4 weeks prior; (6) diagnosis of dialectical spleen or stomach deficiencies or cold syndromes as per TCM; (7) known allergies to trial medications; and (8) pregnant or lactating women and those planning to become pregnant within 6 months after the end of treatment.

##### Withdrawal Criteria

Patients will be withdrawn from the study if they experience serious adverse events, such as nausea, vomiting from oral TCM, or liver and kidney insufficiency, making further observation unsuitable. Additionally, patients who fail to complete the treatment and observation period outlined in the protocol for any reason will be considered for withdrawal. Patients unwilling to continue treatment and requesting to exit the trial will also be withdrawn. Finally, any disease progression that affects or interferes with the study outcomes will result in the withdrawal of the patient from the trial.

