### Assessments

#### Primary Outcomes

In conformity with the NCI-CTCAE version 5.0 and the efficacy assessment criteria in alignment with the *Guiding Principles for Clinical Research on New Chinese Medicine Drugs* [32], the criterion for improvement was defined as a posttreatment rash grade of 0, denoting complete recovery. A ≥2-grade improvement in the rash classification was defined as a marked effect. A single-grade improvement in the rash classification was deemed effective. Should these criteria not be satisfied and the rash either remain unaltered in severity or worsen by more than 1 grade, the treatment will be regarded as ineffective. The following formula will be used: clinical efficacy rate=(cured + significantly improved + improved cases)/total cases × 100% .

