#### Adverse Events

In conformity with the criteria delineated by the Ministry of Health of China’s Adverse Drug Reaction Monitoring Center, as documented in the *Guiding Principles for Clinical Research of New Chinese Medicine Drugs*, the potential relationship between adverse events and the use of the investigational drug will be appraised using a 5-tiered categorization scheme encompassing “certain,” “probable,” “possible,” “remote,” and “unrelated.” The specific evaluation metrics are meticulously outlined in the adverse event table, which is an integral component of the study’s records (Multimedia Appendix 2).

Researchers must prompt patients to honestly report medication effects, steer clear of suggestive questions, and document any adverse reactions on the adverse event form. Follow-up, including detailed records and laboratory test normalization, should continue until symptoms resolve via hospital visits, outpatient checks, or other methods based on reaction severity (Multimedia Appendix 2).

Upon detecting adverse reactions, the researchers will diagnose, treat, and decide whether to halt observation based on the condition. For serious events, the study unit must act promptly to ensure participant safety. Researchers will submit the serious adverse event report form to the oncology department, the ethics committee, and all participating units of the hospital within 24 hours, signing and dating it.

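### The withdrawal rule ends study observation, so day-14 rash grades are lost after randomisation, and the primary efficacy rate does not say how those patients count

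*Protocol article*

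**What the plan says.** The Withdrawal Criteria of the protocol article give four grounds for leaving the trial.

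- Toxicity: "Patients will be withdrawn from the study if they experience serious adverse events, such as nausea, vomiting from oral TCM", continuing "or liver and kidney insufficiency, making further observation unsuitable".
- Non-completion: "patients who fail to complete the treatment and observation period outlined in the protocol for any reason will be considered for withdrawal".
- Patient request: "Patients unwilling to continue treatment and requesting to exit the trial will also be withdrawn".
- Progression: "any disease progression that affects or interferes with the study outcomes will result in the withdrawal of the patient from the trial".

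Under Primary Outcomes the rate is "clinical efficacy rate=(cured + significantly improved + improved cases)/total cases". That section does not say whether the total means patients randomised, treated or graded. It calls treatment ineffective when the rash grade stays the same or worsens, which presupposes a grade after treatment.

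Under Interventions, JDXZ is taken by mouth and urea is applied to the skin. Under Randomization and Blinding, participants know their arm. Under Sample Size, 78 patients are calculated and the number is raised to 94, 47 per arm, for 20% dropout.

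**The concern.** Stopping treatment and stopping observation are different events, and the rule joins them. A patient who stops granules on day 5 can still have the rash graded on day 14, but under this rule is out of the study. A statistical analysis plan can later say how to impute or classify a missing grade. It cannot recover one that was never taken. For that reason the rule belongs in this review even though the analysis plan is not shown.

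The loss happens after randomisation and may depend on both the assigned treatment and its result. One named trigger, nausea or vomiting from an oral medicine, has no counterpart with an ointment. Such patients fit none of the outcome categories, and the denominator does not settle whether they count. At stake is whether the primary comparison remains a comparison of the groups as randomised.

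**Working it through.** **The plan's own figures.** Inputs from Sample Size: 0.8077 and 0.45, alpha .05 (two-sided assumed), power 0.9. The unpooled formula gives n = (1.960 + 1.282)² × (0.8077×0.1923 + 0.45×0.55) / 0.3577² = 33.08 per arm. With continuity correction, n/4 × (1 + √(1 + 4/(n×0.3577)))² = 38.47, so 39 per arm and 78 in total, as stated. Then 78 × 1.2 = 93.6, so 94. The planned dropout of 20% of 47 is 9.4, which is why 9 is used below as a plausible upper number per arm.

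**Effect of leaving withdrawn patients out.** The document gives no withdrawal counts by arm, so these are assumptions. Take 47 per arm, the same true rate p in both arms, and k withdrawn patients in an arm, all of them rash failures. The expected rate among those who remain is p × 47 / (47 − k). The value p = 45% is the planning control rate; 60% is added as a range.

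- p = 45%: k = 9 gives 21.15/38 = 55.7%; k = 5 gives 21.15/42 = 50.4%; k = 0 gives 45.0%.
- p = 60%: k = 9 gives 28.2/38 = 74.2%; k = 5 gives 28.2/42 = 67.1%; k = 0 gives 60.0%.

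The chance of a significant result is the pooled chi-square test at 1.96, by exact binomial enumeration over the remaining patients. Ranges run from p = 45% to p = 60%.

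| Withdrawn JDXZ / urea | False difference, JDXZ minus urea (points) | Significant for JDXZ | Significant for urea |
|---|---|---|---|
| 0 / 0 | 0 | 2.4% | 2.4% |
| 9 / 0 | +10.7 to +14.2 | 16.6% to 28.0% | 0.2% or less |
| 9 / 5 | +5.3 to +7.1 | 7.4% to 10.1% | 0.9% to 0.5% |
| 9 / 9 | 0 | about 2.5% | about 2.5% |
| 5 / 9 | -5.3 to -7.1 | 0.9% to 0.5% | 7.4% to 10.1% |

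**Weaker assumptions.** If 20% of the JDXZ arm and none of the urea arm is withdrawn, but unrelated to rash response, simulation at p = 45% gives a difference of 0.0 points and a two-sided error of 5.1%. If only 5% of the JDXZ arm is withdrawn, all failures, the rate is 21.15/44.65 = 47.4%. The false difference is then +2.4 points, with a simulated two-sided error of 5.9%.

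**The same ambiguity at the planned rates.** Suppose 80.77% and 45% are the rates among those who remain, a difference of 35.8 points. Over all 47 randomised per arm, with withdrawn patients counted as failures:

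- 9 / 0: 0.8077×38/47 = 65.3% against 45.0%, a difference of 20.3 points.
- 9 / 9: 65.3% against 0.45×38/47 = 36.4%, a difference of 28.9 points.
- 0 / 9: 80.8% against 36.4%, a difference of 44.4 points.

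The meaning of the denominator can therefore move the headline result by several points to more than 15.

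**The case against.** Four stronger readings are tempting, and the document supports none of them.

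- *That withdrawn patients are removed from the denominator.* No section says so. If the total means all randomised patients, with the withdrawn counted as non-responders, none of the bias above arises. The analysis set may also be defined in an analysis plan that is not shown.
- *That only JDXZ patients can exit.* Non-completion, request, progression, and liver and kidney insufficiency apply to both arms. Participants know their arm, so urea patients who see no benefit may leave more often, and the sign reverses.
- *That the sample size is built on completers.* Sample Size only adds an allowance for dropout, which is equally compatible with an analysis of everyone randomised.
- *That the Adverse Events section contradicts the withdrawal rule* because it says "Follow-up, including detailed records and laboratory test normalization, should continue until symptoms resolve". Safety follow-up of a reaction can continue after trial assessment ends, so the two can be read together.

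The size is also open to challenge. Vomiting is not a rash outcome, so a patient withdrawn for it need not be a rash failure. The JDXZ-only example is tied to serious events. The eligibility criteria exclude certain spleen and stomach syndromes, and the Introduction reports minimal side effects in the earlier single-arm trial. Nothing shows that a fifth of the JDXZ arm would leave by this route in 14 days. The trial is also described as exploratory.

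All of this limits the direction and size of the bias. It does not answer the point that the rule itself stops the grading.

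**Conclusion.** The point holds in conditional form. The protocol ends study observation for reasons that may relate to treatment and outcome, and the primary endpoint does not say how the affected patients count. If they are left out, the comparison can be biased either way. The one arm-specific trigger would favour JDXZ to the extent that those patients are rash failures.

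The table's range, from about +14 to about -7 points, rests on assumed counts and on every withdrawn patient being a failure. It shows what the wording allows and does not forecast what will happen. The bias is nil when losses are balanced under equal true rates, or unrelated to response. The case for changing the rule is that the change is cheap and that lost grades cannot be recovered at the analysis stage.

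**What to change.** Leave the grounds and timing for stopping treatment as they are, and change what follows.

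1. In the Withdrawal Criteria, separate stopping study treatment from leaving the study. Only withdrawal of consent ends study assessment.
2. Keep the scheduled day-7 and day-14 rash grading for every randomised patient who has not withdrawn consent, and record the reason and date of any early stop by arm.
3. In Primary Outcomes, define the denominator as all randomised patients and count a day-14 grade that is still missing as ineffective.
4. Add a completers analysis and a tipping-point analysis as sensitivity checks. They are needed because counting missing grades as ineffective can itself work against the arm that loses more patients.

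The Results section reports 81 patients enrolled by December 1, 2025, so continued grading can help only patients still within their 14 days or yet to enrol. The denominator and missing-grade rules can still be fixed for everyone before the data are analysed.

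The cost is a few extra assessments after treatment stops, and possibly a less favourable rate in the arm with more early stopping.
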